**Fig. 4 Fig4:**
[figure not shown]
IoT-based hypertension management system satisfaction questionnaire

### Statistical analysis

Statistical analysis will be performed using SPSS 27.0. Normality of continuous variables (e.g., blood pressure values, biochemical indicators) will be assessed using Shapiro-Wilk tests. Normally distributed data will be presented as mean ± standard deviation (x̄ ± s) and analyzed with independent t-tests for between-group comparisons (intervention vs. control) and paired t-tests for within-group changes (baseline vs. follow-up). Non-normally distributed data will be reported as median (interquartile range) and analyzed using Mann-Whitney U test. Categorical variables will be expressed as counts (%) and compared via the chi-square test. A two-sided p-value < 0.05 will indicate statistical significance.

Intention-to-treat analysis will be prioritized [19], with multiple imputation for missing data. Subgroup analyses will be performed for age, hypertension severity, and comorbidity status. In addition, insights on implementation barriers and improvement strategies derived from focus groups and interviews with healthcare professionals will be systematically analyzed using thematic analysis.

The economic evaluation is integrated into the quasi-experimental trial design, comparing the IoT-based hypertension surveillance system (intervention group, IG) with standard care (control group, CG). Costs and outcomes are assessed over a 12-month period to determine incremental cost-effectiveness. The analytical method is Incremental Cost-Effectiveness Ratio (ICER) [20], which is calculated using the following method. Where: ΔC = Change in mean costs (intervention vs. control). ΔE = Change in mean effectiveness (e.g., blood pressure control rate). Bootstrap simulation with 1,000 replications will be conducted to generate ICER distributions, plotted graphically on cost-effectiveness planes.$$\:ICER=\frac{\left({\Delta\:}{C}_{IG}-{\Delta\:}{C}_{CG}\right)}{\left({\Delta\:}{E}_{IG}-{\Delta\:}{E}_{CG}\right)}$$

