### Sample size calculation

A formal power calculation was performed a priori using G*Power software (version 3.1.9.7) for the primary outcome: the between-group difference in blood pressure control rate.

The anticipated control rate in the control group (P₁) was conservatively estimated at 45%, informed by historical data from our health center and findings from literature on usual care in similar settings [16]. We hypothesized that the IoT-based intervention would yield a clinically meaningful absolute improvement of 10% points, raising the control rate in the intervention group (P₂) to 55%. This effect size is supported by a recent meta-analysis of mHealth interventions [16], which reported a significant absolute improvement yet considerable heterogeneity among studies.

Using a two-sided significance level (α) of 0.05 and a power (1-β) of 80%, the calculation indicated a minimum requirement of 350 participants per group (total *n* = 700). Accounting for an estimated 15% attrition rate, the sample size was adjusted to 412 per group (total *n* = 824).

However, considering that there are more than 80,000 hypertension patients in this region and approximately 20,000 hypertension patients who have signed contracts with family doctors in this community, in order to achieve better research results and based on the available research resources, it was finally decided to include 2,000 patients, with 1,000 patients in the intervention group and 1,000 patients in the control group. This larger sample size ensures robust power for the primary and all secondary outcomes, enables precise subgroup analyses, and provides high-quality, generalizable evidence essential for informing public health policy on chronic disease management.

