### Outcomes and variables

The primary outcome of the trial is blood pressure control rate, which is the proportion of patients whose blood pressure is maintained within the target range. According to the National Basic Public Health Service Specification (Third Edition) [15], blood pressure should be controlled below 140/90 mmHg for individuals aged 35–65 years, and below 150/90 mmHg for those aged 65 years and above. Secondary outcomes: (1) standardized management rate: Calculated as the proportion of patients in the intervention and control groups who receive management in accordance with the National Basic Public Health Service Specification (Third Edition) [15], to evaluate the impact of the system on the standardization of hypertension management; (2) blood pressure measurement completion rate: The number of blood pressure measurements completed per patient compared to the expected quarterly measurements; (3) Referral rates: The number of patients referred to higher-level hospitals due to refractory or secondary hypertension, and the proportion of referred patients whose blood pressure stabilizes upon return; (4) Biochemical indicators: Changes in lipid profiles and other relevant biomarkers.

In addition, exploratory outcomes are economic evaluation(cost-effectiveness: analysis of system deployment costs versus improvements in hypertension control and reduced referrals; performance incentives: correlation between system-generated data and family doctor contract fulfillment metrics for incentive allocation), patient satisfaction (the subjective experiences and perceived effects), implementation barriers (engage professionals in focus groups and interviews to examine implementation barriers and improvement opportunities from the service providers’ perspective).

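### A Shapiro-Wilk pre-test chooses between mean and rank comparisons for the continuous secondary variables, and neither branch adjusts for the baseline values that are collected

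*Protocol article*

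**What the plan says.** The protocol article, Statistical analysis, sets a rule for continuous variables: "Normality of continuous variables (e.g., blood pressure values, biochemical indicators) will be assessed using Shapiro-Wilk tests". Data judged normal are summarised by mean and SD and "analyzed with independent t-tests for between-group comparisons (intervention vs. control) and paired t-tests for within-group changes (baseline vs. follow-up"). For the rest, "Non-normally distributed data will be reported as median (interquartile range) and analyzed using Mann-Whitney U test". No level is given for the pre-test, and no paired test is named for non-normal data.

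The primary outcome is a proportion and takes another route: "Categorical variables will be expressed as counts (%) and compared via the chi-square test".

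Outcomes and variables lists one clearly continuous secondary outcome, the biochemical indicators: "Changes in lipid profiles and other relevant biomarkers". Measurement completion per patient could be treated as another. Continuous blood pressure is not a listed outcome, but the analysis section names it as an example of a variable to be tested for normality.

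Study conduct collects blood pressure and fasting laboratory values at baseline. The Participants section matches controls on age, sex and hypertension duration. The Discussion concedes that allocation is not randomised and may bring selection bias. Sample size calculation fixes the final size, "with 1,000 patients in the intervention group and 1,000 patients in the control group", and assumes 15% attrition.

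**The concern.** A normality test answers the wrong question at this size. Its power grows with n, so it flags departures too small to matter, while the t-test becomes less sensitive to non-normality as n grows. The choice between a mean and a rank comparison then depends on sample size, rounding and chance. The same marker could be compared by ranks in the full sample and by means in one of the planned subgroups.

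The second issue is independent of the first. Both branches are unadjusted. In a comparison of different sites, where baseline blood pressure and laboratory values are measured but not matched, any baseline difference stays in a follow-up-only comparison, and precision is given away. At stake are the size and interpretability of the secondary effect estimates.

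**Working it through.** **The plan's own figures.** The documents give no figure for the pre-test. The input that matters is the number per arm: 1,000, or 1,000 × 0.85 = 850 after attrition. The stated minimum of 350 per group (45% v 55%, two-sided 5%, 80% power) does not reproduce. The pooled formula gives [1.96√(2 × 0.5 × 0.5) + 0.842√(2 × 0.45 × 0.55)]² / 0.10² ≈ 392, and 350 gives 75.5% power. That concerns the binary primary outcome, which has 99.4% power at 1,000 per arm and 98.5% at 850, and it has no bearing here.

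**Step 1: how often the gate rejects.** The documents give no distributions, SDs or correlations, so those below are assumptions. The pre-test level is taken as 5%, with 600 simulated samples per cell (Monte Carlo standard error at most √(0.25/600) = 2 percentage points).

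| Assumed variable | n = 50 | n = 850 | n = 1,000 |
|---|---|---|---|
| Exactly normal | 5% | 7% | 5% |
| Systolic, normal, SD 15, rounded to 1 mmHg | 5% | 9% | 11% |
| Diastolic, normal, SD 9, rounded to 1 mmHg | 4% | 20% | 25% |
| Systolic, rounded to 2 mmHg | 6% | 40% | 50% |
| Gamma, skewness 0.2 | 6% | 57% | 65% |
| Lognormal, CV 10% | 12% | 88% | 93% |
| Lognormal, CV 15% | 20% | 100% | 99.8% |
| Lognormal, CV 20% | 33% | 100% | 100% |
| Change between two lognormals, CV 25%, r = 0.6 | 11% | 75% | 79% |

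The lognormal variable with CV 10% is rejected 12% of the time at n = 50 and 93% at n = 1,000, so sample size drives the result.

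**Step 2: does the t-test need protection?** With lognormal data of CV 50% and 850 per arm, the simulated type I error of the two-sample t-test is 4.5% (4,000 replicates) against a nominal 5%. It does not.

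**Step 3: does the gate itself cost power?** For a 0.10 SD effect and 1,000 per arm, the unadjusted t-test has non-centrality 0.10 × √(1,000/2) = 2.24 and power Φ(2.24 − 1.96) ≈ 61%. Simulated Mann-Whitney power on follow-up values is about 58-62%. The two branches are about equal.

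**Step 4: what adjustment gains.** With equal variances at both times and baseline to follow-up correlation r, the variance of the baseline-adjusted estimate is (1 − r²) times that of a follow-up-only comparison. It is (1 − r²) / [2(1 − r)] = (1 + r)/2 times that of a change-score comparison.

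| r | v follow-up only | v change score |
|---|---|---|
| 0.3 | 0.91 | 0.65 |
| 0.5 | 0.75 | 0.75 |
| 0.6 | 0.64 | 0.80 |

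Illustration with assumed SD 15, true difference 2 and 850 per arm: follow-up-only power is 78%; change-score power is 64%, 78% and 87% at these three r; adjusted power is 82%, 89% and 93%.

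**Step 5: baseline imbalance.** Suppose the arms differ by 2 mmHg at baseline, r = 0.5, and there is no effect given baseline. A follow-up-only comparison then expects a spurious difference of 2 × 0.5 = 1.0 mmHg. With SD 15 and 850 per arm (standard error 15√(2/850) = 0.73) it is declared significant about 28% of the time.

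**The case against.** The strongest reply is that both branches are valid between-group tests at this size, the affected outcomes are secondary, and covariate lists and transformations usually sit in a statistical analysis plan that is not shown. The first two points stand and limit the weight of this one. The third does not dispose of it: the gate is a stated method, not an omitted detail, and a later plan would have to reverse it.

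Four stronger readings are tempting and should be resisted.

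- A reader might infer that nearly all continuous outcomes will go to Mann-Whitney. The documents give no distributions, and for near-normal blood pressure rejection is only about 11-50% at 1,000 per arm. Near-certain rejection applies to clearly skewed laboratory values.
- A reader might infer that the plan ignores baseline. The biochemical outcome is defined as change, which uses baseline by subtraction. The article does not say whether follow-up values or changes enter the between-group test. The accurate statement is that there is no adjustment for baseline.
- A reader might blame the gate for lost power. Step 3 shows that it costs almost none; the loss comes from the missing adjustment, which the t-test branch shares.
- A reader might infer that Mann-Whitney will be run on paired data. At r = 0.5 that would give a type I error of about 0.6%, from 2P(Z > 1.96/√0.5). The text, however, only leaves a gap, which a condensed article may well do. It also concerns within-group tests, not the treatment effect.

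It is also fair to say that if a variable is rejected almost always, its branch is hardly data-dependent. That holds for skewed laboratory values. The choice is open for near-normal variables and for change scores such as the one rejected 79% of the time.

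**Conclusion.** The point holds for the continuous secondary variables: chiefly the biochemical changes, and blood pressure values where they are compared. The primary outcome is untouched, so this should be changed but does not threaten the main result.

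Two conclusions stand separately. The pre-test protects against nothing in the conditions examined and leaves the choice between mean and rank comparison to the data. And neither branch adjusts for baseline blood pressure or laboratory values in a non-randomised comparison matched only on age, sex and hypertension duration. Adjustment cuts variance by 9-36% against a follow-up-only comparison and by 20-35% against a change score over r = 0.3 to 0.6, so it helps under either reading of the outcome.

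The rule and the missing adjustment are read from the text. The sizes rest on assumed distributions, SDs, correlations and a 5% pre-test level. Adjustment reduces imbalance in measured baseline values; it does not remove unmeasured confounding.

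**What to change.** Delete the normality gate. For each continuous outcome with a baseline value, pre-specify a linear model of the follow-up value on group and baseline value, plus age, sex and hypertension duration, with robust standard errors. Name in advance the markers expected to be skewed, and log-transform both their baseline and follow-up values. Report the adjusted difference, or ratio for logged markers, with its 95% CI.

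This also settles whether follow-up or change is analysed: on a given scale, with baseline in the model, the group coefficient is the same for both. It supplies the estimate and standard error that the planned multiple imputation has to pool.

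Keep Mann-Whitney as a sensitivity analysis. If within-group tests of non-normal data are kept, name the signed-rank test.

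The cost is a few sentences in the analysis section, best settled before outcome data are examined. No new data are needed, because the baseline values are already collected.

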### Participants, selection criteria and recruitment

The study targets hypertensive patients managed under the family doctor contract service at Liyuan Community Health Center and its subordinate Community Health Station in Tongzhou District, Beijing. The intervention group (IG) will consist of 1,000 hypertensive patients randomly selected from five family doctor teams at Liyuan Community Health Center and subordinate Xiaogao Station where the IoT-based hypertension monitoring system is deployed. The control group (CG) will include another 1,000 hypertensive patients from other stations without the system, matched for baseline characteristics.

Participants must meet the following inclusion criteria to be enrolled in the study. First, they must be aged 35 years or older and have a confirmed diagnosis of primary hypertension as defined by the Chinese Hypertension Clinical Practice Guidelines [17], which requires systolic blood pressure ≥ 140 mmHg and/or diastolic blood pressure ≥ 90 mmHg measured on at least two separate occasions to ensure diagnostic accuracy. Second, they must be residents within the administrative jurisdiction of Liyuan Health Center and have signed a family doctor contract, which is a prerequisite for accessing hypertension management services under the National Basic Public Health Service Program [18]. This ensures that participants are eligible for the standardized care and monitoring provided by the health center’s healthcare teams. Third, participants must demonstrate the functional capacity to attend outpatient visits either independently or with minimal assistance, excluding those who are bedridden or require full-time care. This criterion is essential to ensure that participants can engage in regular blood pressure measurements, follow-up consultations, and health assessments as required by the study protocol, thereby facilitating the collection of reliable data on hypertension management outcomes.

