Participants will be excluded if they meet any of the following criteria to ensure the safety and validity of the research results. First, individuals with a history of acute cardiovascular or cerebrovascular events, such as stroke, myocardial infarction, or aortic disease, occurring within the past 12 months are excluded, as these conditions may confound the assessment of hypertension management outcomes and require specialized clinical interventions that could interfere with the study’s standardized procedures. Second, participants with severe comorbidities, including heart failure, severe renal failure, or cancer, are ineligible, as their complex medical conditions may reduce their capacity to adhere to the study’s monitoring protocols and could lead to substantial variability in health-related outcomes. Third, individuals with uncontrolled psychiatric conditions (such as schizophrenia or severe depression with suicidal ideation) will be excluded, as these conditions may compromise study participation, data accuracy, or patient safety. Fourth, patients aged over 80 years or those with severe mobility impairment (defined as the inability to ambulate even with assistive devices) are excluded, as their limited physical capacity may hinder regular attendance and adherence to the study’s follow-up schedule. Finally, pregnant or lactating females are excluded due to the unique physiological changes and medication considerations during this period, which require specialized care outside the scope of the study’s focus on primary hypertension management in the general adult population. These exclusion criteria are designed to minimize confounding variables and ensure that the results reflect the true impact of the intelligent monitoring system on hypertension patients under routine primary care settings.

Eligible participants will be identified through Liyuan Health Center’s electronic health record (EHR) system, which maintains a registry of approximately 20,000 registered hypertension patients. The research team will use EHR data to pre-screen candidates, filtering for age, diagnosis, contract status, and exclusion criteria, after which random selection will be performed using a computer-generated random number table, stratified by age and sex to ensure demographic balance. Meanwhile, the control group (CG) will match to the intervention group (IG) on age, sex, and hypertension duration using EHR data to minimize baseline confounding.

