### Study conduct

Eligible patients will be recruited via text messages or in-person during clinic appointments, explaining the study objectives, procedures, and voluntary nature of participation. Those interested will be contacted by research nurses for a telephone or in-person consultation to review the study details, including risks, benefits, and data confidentiality. Written informed consent will be obtained prior to enrollment. Upon consent, participants will complete a baseline assessment comprising: (1) demographics (age, sex, education); (2) clinical metrics: blood pressure (measured twice at rest, 5 min apart), BMI, fasting labs for lipids/glucose/renal/liver function, duration of hypertension, known comorbidities (e.g., diabetes, coronary artery disease); (3) functional assessment: mobility status (e.g., walking ability, use of assistive devices) and adherence to hypertension management (e.g., medication compliance, clinic visit frequency).

Following blood pressure measurement, the intervention group’s data will be automatically transmitted to the electronic health record system via IoT-enabled devices, where values are instantly integrated into statistical analyses and visualized on clinic display screens for real-time monitoring by both clinicians and patients. The system will trigger alerts for uncontrolled hypertension (systolic blood pressure is greater than 180 mmHg or diastolic blood pressure is greater than 110 mmHg [17]), enabling timely clinical decisions (medication adjustments/referrals). Participants will receive printed personalized reports with trend analyses and educational materials after each measurement. The control group will receive standard care via traditional health huts without IoT integration, with data manually recorded in electronic health records.

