## Discussion

This study represents one of the first attempts to evaluate the effectiveness of an IoT-based hypertension surveillance system in primary healthcare settings in China. The integration of real-time monitoring, automated data analysis, and dynamic performance evaluation tools addresses critical gaps in traditional hypertension management, such as fragmented data collection and low patient adherence. By combining quantitative outcomes (e.g., blood pressure control rates) with qualitative insights from patients and healthcare providers, the study offers a comprehensive understanding of the system’s feasibility and impact.

A key strength of this study lies in its pragmatic quasi-experimental design, which reflects real-world conditions by evaluating an existing intervention within routine clinical practice. The large sample size (*n* = 2000) and rigorous baseline matching enhance the generalizability of the findings to similar urban and suburban primary care settings. Additionally, the inclusion of cost-effectiveness analysis provides valuable evidence for policymakers to allocate resources efficiently.

However, several limitations should be acknowledged. First, the non-randomized allocation of participants (due to the pre-existing deployment of the IoT system in selected locations) may introduce selection bias. Although baseline matching will be used to mitigate confounding, unmeasured variables (e.g., socioeconomic status) could influence outcomes. In addition, the study’s reliance on electronic health records for control group data may lead to inconsistencies in data quality compared to the IoT system’s automated measurements.

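### The primary comparison of blood pressure control between non-randomised, site-defined groups is unadjusted, so a baseline gap between sites biases it to the extent that the gap persists

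*Protocol article*

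**What the plan says.** All references are to the Protocol article.

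- **Allocation.** Intervention patients come from five family doctor teams at the health centre and one station where the system runs; controls come from other stations. The Discussion accepts that "the non-randomized allocation of participants (due to the pre-existing deployment of the IoT system in selected locations) may introduce selection bias".
- **Matching.** Participants, selection criteria and recruitment first says that the control group "will include another 1,000 hypertensive patients from other stations without the system, matched for baseline characteristics". It later names the characteristics: "the control group (CG) will match to the intervention group (IG) on age, sex, and hypertension duration using EHR data". Blood pressure, control status, comorbidity and adherence are not among them.
- **Baseline data.** Study conduct collects blood pressure, comorbidities, education and "adherence to hypertension management (e.g., medication compliance, clinic visit frequency".
- **Primary outcome.** In Outcomes and variables, the definition begins: "The primary outcome of the trial is blood pressure control rate, which is the proportion of patients whose blood pressure is maintained within the target". This is binary for each patient.
- **Tests.** In Statistical analysis, normally distributed continuous data are "analyzed with independent t-tests for between-group comparisons (intervention vs. control) and paired t-tests for within-group changes (baseline vs. follow-up". Non-normal data go to the Mann-Whitney test. Categorical data are given as counts and percentages and compared by chi-square; that sentence governs the primary outcome. No regression, baseline adjustment, propensity method or site term is named for the clinical outcomes.

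**The concern.** A crude chi-square test suits individually randomised groups, where baseline differences arise by chance and the p-value allows for them. Here group membership follows location. If control was already better or worse at the sites with the system, whatever part of that gap remains at follow-up is counted as an effect of the system.

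Matching on three demographic and duration variables does not balance baseline blood pressure, which can be expected to predict later control strongly. The data needed to deal with this are already collected, but the named between-group tests cannot use them. Enlarging the sample to 2,000 does not help: it narrows the confidence interval around a biased estimate.

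The same holds for the t-tests and Mann-Whitney tests of continuous outcomes, unless they are run on changes from baseline. The within-group paired tests compare each group with its own baseline, so they do not repair the between-group comparison.

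**Working it through.** **Inputs from the Protocol article (Sample size calculation):** control rate 45%, target 55%, two-sided α 0.05, 80% power, 1,000 per group, 15% attrition (850 per group remaining). **Assumed, because the documents do not give them:** the size of the baseline gap and how far it persists.

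**1. The plan's own figure.** For 45% against 55%:

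n = [1.96·√(2·0.5·0.5) + 0.8416·√(0.45·0.55 + 0.55·0.45)]² / 0.10² = (1.386 + 0.592)² / 0.01 ≈ 392 per group.

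The article states 350, which does not reproduce; its attrition step does (350/0.85 = 412). This has no bearing here, because 1,000 per group gives 99.4% nominal power.

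**2. Smallest difference that reaches p<0.05.** 1.96·√(2·0.475·0.525/n) is 4.4 points at n = 1,000 and 4.7 at n = 850. Both are less than half the 10-point target.

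**3. Rejection probability of the unadjusted test with no treatment effect.** For a gap d still present at follow-up:

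P = 1 − Φ[(1.96·SE₀ − d)/SE₁] + Φ[(−1.96·SE₀ − d)/SE₁], where SE₀ is the pooled and SE₁ the unpooled standard error.

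For 45% against 50% at n = 1,000: SE₀ = √(2·0.475·0.525/1000) = 0.02233 and SE₁ = √((0.45·0.55 + 0.50·0.50)/1000) = 0.02230. Then (0.04377 − 0.05)/0.02230 = −0.28, so P ≈ 0.61.

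| Gap remaining at follow-up | n = 1,000 | n = 850 |
|---|---|---|
| 0 points | 5% | 5% |
| 2 points | 15% | 13% |
| 3 points | 27% | 24% |
| 5 points | 61% | 54% |
| 7 points | 88% | 82% |

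**4. How much of a 5-point baseline gap remains.** Two scenarios bracket the question.

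- *The gap acts only through each patient's own baseline status.* With 45% controlled at both times, the remaining gap is r × 5 points, where r is the correlation between baseline and 12-month control. For r = 0.4 this is 2.0 points, rejected about 15% of the time; for r = 0.5 it is 2.5 points, about 20%. A 1,000-run simulation with 12-month control of 75% if controlled at baseline and 20.5% if not (r = 0.75 − 0.205 = 0.545) leaves 2.7 points and rejects 21.5%. A 10-point baseline gap in that simulation leaves 5.5 points and rejects 70%.
- *The gap persists in full.* All 5 points remain, and the test rejects 61% of the time.

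**5. What adjustment does.** Logistic regression on group and baseline control status:

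- First scenario: rejection falls to 5.3% (5.0% for the 10-point gap).
- Second scenario: baseline status explains only r × 5 points, so 5 − 2.0 = 3.0 points (r = 0.4) to 5 − 2.5 = 2.5 points (r = 0.5) remain. Simulated rejection is about 31% and 26%, and down to about 23% across the runs made.

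**6. What a difference-in-differences does.** It subtracts the whole baseline gap. In the second scenario the bias is 5 − 5 = 0. In the first it overcorrects by r × 5 − 5, which is −3.0 to −2.5 points. The two estimates thus rest on opposite assumptions about persistence and are informative together.

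All figures treat patients as independent; clustering by team or site is a separate matter.

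**The case against.** **A full analysis plan may exist.** The article is a condensed account, and silence on covariates would be no finding. But it is not silent: it names the between-group tests, and none of them can adjust. The Discussion discloses selection bias and says that "unmeasured variables (e.g., socioeconomic status) could influence outcomes". It offers only matching in response, and does not mention that measured baseline blood pressure is left out of the comparison. Disclosure does not change the stated analysis.

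**Baseline information is not unused throughout.** Subgroup analyses by severity and comorbidity are planned, biochemical outcomes are defined as changes, and the ICER formula subtracts change terms with control rate as its example. This stands. None of it adjusts the primary chi-square test. It also means that the clinical and economic analyses could give different effects on the same outcome if baseline control differs.

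**Stronger readings that the documents do not support:**

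- A reader might infer that any baseline gap passes whole into the result, so that 27%, 61% and 88% are the expected error rates for 3, 5 and 7 points. Those apply only under full persistence, and the documents give neither a gap nor its persistence.
- A reader might infer that the plan treats within-group paired tests as evidence of effect. It assigns between-group comparisons to the independent tests.
- A reader might infer that the groups should be rematched on recorded control status. The Discussion describes deployment as pre-existing, so those records may already reflect exposure, and matching unlike sites on a prior outcome can induce regression to the mean.
- A reader might infer that covariate adjustment cures the problem. Site coincides with treatment, so it cannot.

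**Conclusion.** The point holds in conditional form. The article fixes an unadjusted comparison of the primary outcome between site-defined groups that are not matched on baseline blood pressure, while collecting the data that would allow adjustment. The direction and size of the resulting bias are unknown.

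For an assumed 5-point baseline gap, no true effect and 1,000 independent patients per group, the false-positive rate is about 15–22% if the gap acts only through individual baseline status and 61% if it persists in full, against a nominal 5%. Adjustment for baseline status brings these to about 5% and about 23–31%. It is therefore a clear improvement using data already collected, but not a remedy for site confounding. It matters because it concerns the primary estimate, and a choice of adjustment made after outcomes are seen would carry little weight.

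**What to change.** - Make the primary analysis a logistic regression of blood pressure control on group, baseline blood pressure or control status, age, sex, hypertension duration, comorbidity, education and baseline adherence. Report a marginal risk difference with its confidence interval.
- For continuous outcomes, use linear models adjusted for the baseline value.
- Add a difference-in-differences estimate of the change in control rate as a sensitivity analysis for a stable site gap. This agrees with the change terms already in the ICER formula.
- State that adjustment reduces but does not remove site confounding, and base claims of effect on the between-group estimate, not on the within-group paired tests.

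The matching variables need not change. The cost is analysis wording: every covariate is already in the baseline assessment. Under the Ethics section, protocol modifications go to further ethics review as necessary, so the change should be made and dated before outcome data are examined.
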